**Figure 1 figure1:**
[figure not shown]
The Empatica E4 device.

**Table 1 table1:** Schedule of events for Remote Assessment of Disease and Relapse Epilepsy.

Events		Weeks (months)												
		0 (0)	2 (0)	4 (1)	6 (1)	8 (2)	10 (2)	12 (3)	14 (3)	16 (4)	18 (4)	20 (5)	22 (5)	24 (6)
Visit		1 (Baseline)	—^a^	2 (Follow-up)	—	—	—	3 (Follow-up)	—	—	—	—	—	4 (Study end)
**Assessment**														
	Study explanation	✓^b^	—	—	—	—	—	—	—	—	—	—	—	—
	Informed consent	✓	—	—	—	—	—	—	—	—	—	—	—	—
	Introductory training (60 min)	✓	—	—	—	—	—	—	—	—	—	—	—	—
	Sociodemographics	✓	—	—	—	—	—	—	—	—	—	—	—	—
	Medical history	✓	—	—	—	—	—	—	—	—	—	—	—	—
	Study debrief	—	—	—	—	—	—	—	—	—	—	—	—	✓
	Monitoring telephone call	—	✓	—	✓	✓	✓	—	✓	✓	✓	✓	✓	—
	Qualitative interview	—	—	✓	—	—	—	✓	—	—	—	—	—	✓
	TAM-FF^c^	—	—	✓	—	—	—	✓	—	—	—	—	—	✓
	PSSUQ^d^	—	—	✓	—	—	—	✓	—	—	—	—	—	✓
**Passive RMT ^e^**														
	Wearable sensors	—	—	—	—	—	—	Continuous	—	—	—	—	—	—
	Smartphone sensors	—	—	—	—	—	—	Continuous	—	—	—	—	—	—
**Active** **RMT**														
	Seizure diary and precipitants	—	—	—	—	—	—	Daily questionnaire	—	—	—	—	—	—
	ESM^f^ assessment	✓	—	—	✓	—	—	✓	—	—	✓	—	—	✓
	Cognition	✓	—	—	✓	—	—	✓	—	—	✓	—	—	✓
	Speech task	✓	✓	✓	✓	✓	✓	✓	✓	✓	✓	✓	✓	✓
	Mood PHQ8^g^ (A^h^)	✓	✓	✓	✓	✓	✓	✓	✓	✓	✓	✓	✓	✓
	Anxiety GAD7^i^ (A or W^j^)	✓	—	—	—	—	—	✓	—	—	—	—	—	✓
	Self-esteem RSES^k^ (A)	✓	—	—	—	—	—	✓	—	—	—	—	—	✓
	Quality-of-life WSAS^l^ (A or W)	✓	—	—	—	—	—	✓	—	—	—	—	—	✓
	BIPQ^m^ (A or W)	✓	—	—	—	—	—	✓	—	—	—	—	—	✓
	Change in medications (T^n^ or F2F^o^)	—	—	✓	—	—	—	✓	—	—	—	—	—	✓
	CSR^p^ (T or F2F)	—	—	✓	—	—	—	✓	—	—	—	—	—	✓
	LTE-Q^q^ (T or F2F)	—	—	✓	—	—	—	✓	—	—	—	—	—	✓

^a^—: Task or assessment not required.

^b^✓: Task or assessment required.

^c^TAM-FF: Technology Assessment Model Fast Form.

^d^PSSUQ: Post-Study System Usability Questionnaire.

^e^RMT: remote measurement technology.

^f^ESM: experience sampling method.

^g^PHQ8: 8-item Patient Health Questionnaire.

^h^A: assessed via app.

^i^GAD7: 7-item Generalized Anxiety Disorder questionnaire.

^j^W: web-based assessment.

^k^RSES: Rosenberg Self-esteem Scale.

^l^WSAS: Work and Social Adjustment Scale.

^m^BIPQ: Brief Illness Perceptions Questionnaire.

^n^T: telephone assessment.

^o^F2F: face to face assessment.

^p^CSRI: Client Service Receipt Inventory.

^q^LTE-Q: List of Threatening Experiences Questionnaire.

### Study Procedures

Participants will be recruited over 6 months from the Epilepsy Service and Clinical Neurophysiology Department at King’s College Hospital, London, and from the Epilepsy Center, Department of Neurosurgery, University of Freiburg, Germany.

Potentially eligible individuals will be identified among those attending a routine outpatient appointment or hospital video–EEG EMU admission or home video–EEG monitoring appointment at the participating sites. These individuals will be approached by a member of the on-site research team and given the study information sheet and consent form.

### Study Overview

The study schedule of events and assessments is detailed in Table 1.

After a minimum of 24 hours from the time they receive the study information sheet and consent form, the research team will contact the potential participant to assess their interest in taking part in the study. Following a positive response, a first visit will be scheduled for them at the research center to confirm eligibility, discuss the study, explain study procedures, answer any questions, and obtain written informed consent. Sociodemographic information, medical history, and baseline data will be collected (Table 1).

Participants will also receive a 60-min introductory training session on the use of the wearable device and will be assisted in downloading the apps. A leaflet summarizing key information will be provided. At the end of the training session, study participants will be asked to start wearing the device, and active and passive recording of data will begin. Participants will receive a follow-up call 2 weeks after the start of data recording to provide any additional support as required (Table 1).

After this, participants will attend a follow-up visit after 1 and 3 months (visits 2 and 3), where primary outcomes (as given in the *Study Outcomes* section) will be assessed. At visit 4 (study endpoint), participants will be invited to have a last face-to-face meeting to assess outcomes. A debrief session of 60 min will take place at visit 4, and acceptability and usability of the technology will be assessed with a qualitative interview and questionnaires (as given in the *Study Outcomes* section).

### Study Outcomes

The primary outcome of interest was participants’ acceptability and usability of the RADAR technology, including the wearable, the apps, and the assessment scheme. Acceptability and usability will be evaluated using the Post-Study System Usability Questionnaire (PSSUQ) [46]; the Technology Assessment Model Fast Form (TAM-FF) [47]; and ad hoc created qualitative interviews undertaken at 1, 3, and 6 months postenrollment. Participants who dropped out before the study endpoint will be contacted to complete an interview.

Secondary outcomes include (1) sensitivity and false alarm rate of the device, as compared with patient seizure diary, for different seizure types: generalized tonic-clonic seizures, focal seizures (FS) with motor features, FS with autonomic features, and FS with dyscognitive features and (2) identification of variables influencing the long-term trajectory of seizure frequency: pRMT features (measured through the wearable sensors and smartphone sensors), and aRMT assessments, including comorbidities, seizure precipitants, ESM, speech, and cognitive functions.

### Contextual Variables

Variation in self-esteem will be measured using the Rosenberg Self-Esteem Scale [48], a 10-item self-reported questionnaire. QoL or disability will be measured using the Work and Social Adjustment Scale [49], a 5-item assessment of perceived social and work-related functional impairment used widely across a range of mental and physical disorders. Illness perceptions will be assessed using the Brief Illness Perceptions Questionnaire [50], which provides an insight into participants’ views about their underlying conditions, including a measure of how well they see themselves coping with its symptoms and treatments.

We will seek to identify major changes in participants’ circumstances that may materially affect participants’ outcomes and may also impact the use of RMT. In particular, we will collect information about change in medications for epilepsy, health service utilization (the modified Client Service Receipt Inventory [CSRI]) [51], and change in life circumstances (List of Threatening Experiences Questionnaire [LTE-Q]) [52].

### Study Monitoring

In addition to evidence of the acceptability and usability of the RADAR technology, data obtained throughout the course of the study will be used to make iterative developments to the platform software and to the questionnaire schedule and to optimize the usability of the system. During the scheduled monitoring telephone calls, the correct use of device and apps will be assessed to identify whether a loss of data is because of potential technical or practical issues that can be resolved. Participants’ problems, concerns, and questions will also be discussed to facilitate engagement and to support adherence to the protocol. These contacts will be recorded as evidence of feasibility and acceptability outcomes. The research team will systematically review upcoming data and may decide to schedule additional monitoring telephone calls if some discrepancies were found during the data collection and streaming.

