## Methods

### Study Design and Population

This study is a multicenter, prospective, observational, nonrandomized, and noninterventional cohort study in which 32 individuals with a diagnosis of epilepsy will be asked to download several RMT apps and use a wearable device for up to 6 months of follow-up. The inclusion and exclusion criteria are provided in Textboxes 1 and 2, respectively.

Inclusion criteria.Inclusion criteriaAble to give informed consent for participationDiagnosis of epilepsyAged between 18 and 70 yearsMinimum average seizure frequency of 2 seizures per monthWilling and able to complete self-reported assessments via smartphonesFluent in English (German in Freiburg) and able to read and write English (German in Freiburg)Willing to continuously wear the study wearable deviceExisting ownership of an Android smartphone (or willingness to use an Android smartphone, which will be provided as their only smartphone)Existing ownership or the possibility of connecting to a Wi-Fi connection on a daily basis

Exclusion criteria.Exclusion criteriaEstablished diagnosis of psychogenic nonepileptic attacks (dissociative seizures) as the only seizure typeFrequent vigorous involuntary movements (eg, chorea and athetosis) or frequent parasomnias with major motor components (eg, sleep walking and night terrors)Inability to comply with the trial procedure, such as cognitive or behavioral problemsInability to give informed consentUnwillingness to use an Android smartphone

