### Statistical Analysis Plan

Descriptive statistics for demographics, attrition rate, and number of participants using remote assessment measurements will be estimated. The primary outcome measurement (PSSUQ and TAM-FF) will be analyzed using a mixed-effect model for repeated measures based on observed case data. The model will include the duration in the study and contextual variables (CSRI, LTE-Q, etc) as covariates. Using classification approaches, we will investigate whether any demographics and/or other numerical information might serve as a predictor for subjects dropout. Using mixed-effect models with participants as a random factor, we will estimate whether there is a univariate relationship between the amount of RMT usable data during the weeks before the outcome assessment and obtained scale measurements (PSSUQ and TAM-FF). Acoustic features such as pitch, jitter, shimmer, formants, and intensity of the voice will be extracted from the speech task and will be analyzed.

To assess seizure detection performance of a multiparametric wearable system, we will relate seizures detected by the wearable system to the information from the seizure diary, kept by each participant. We will estimate the sensitivity of seizure detection by the wearable system (ie, whether all seizures reported in the diary were detected by wearable system) and false alarm rate (ie, number of seizures detected by the wearable system but not reported in the diary per unit of time, eg, day).

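### If in-study software and schedule changes reach enrolled participants, the duration effect on usability mixes time in study with release, and the stated model has no release term

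*Protocol article*

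**What the plan says.** Four places in the protocol article bear on this.

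- **Study Outcomes.** The primary outcome is "participants’ acceptability and usability of the RADAR technology, including the wearable, the apps, and the assessment scheme". Interviews are "undertaken at 1, 3, and 6 months postenrollment", and Table 1 puts the PSSUQ and TAM-FF at the matching visits, weeks 4, 12 and 24.
- **Study Monitoring.** "data obtained throughout the course of the study will be used to make iterative developments to the platform software and to the questionnaire schedule", and the purpose is "to optimize the usability of the system".
- **Statistical Analysis Plan.** PSSUQ and TAM-FF "will be analyzed using a mixed-effect model for repeated measures based on observed case data". The covariates follow: "The model will include the duration in the study and contextual variables (CSRI, LTE-Q, etc) as covariates".
- **Contextual Variables.** The variables described are self-esteem, quality of life or disability, illness perceptions, medication changes, service use and life events. Software version and schedule version are not among them, so the open-ended list in the model does not obviously take them in.

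The article gives no release dates, no number of releases and no rule on when a change may be deployed.

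**The concern.** Two of the three rated components, the apps and the assessment scheme, may be altered during the study in order to improve the quantity the primary outcome measures. The model describes change through duration in study alone. If a release improves the scores of people already in follow-up, the model attributes that gain to time in study. If tolerance of the device declines while the software improves, the two can cancel and the trend looks flat. A score pooled over visits, or taken at month 6, averages over whichever versions were in use.

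What is at stake is the interpretation of the primary result: whether a change between months 1 and 6 says something about living with the system, or about the system having been changed.

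**Working it through.** The plan attaches no power, alpha or effect size to its sample size, so there is no figure to reproduce. The check asks how far duration and release can be told apart, and what happens when release is left out.

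**Inputs from the article**
- Sample size: "32 individuals with a diagnosis of epilepsy will be asked to download several RMT apps", so n = 32.
- Assessments at months 1, 3 and 6.
- Entry: "Participants will be recruited over 6 months". Six months of entry plus six of follow-up is 12 months, which agrees with data collection from 30 September 2020 to 30 September 2021.

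**Assumptions not in the article**
- Entry uniform over 6 months.
- Simulation only: between-person SD 0.8 and residual SD 0.6 (total variance 0.64 + 0.36 = 1, so points equal SDs), and a true duration effect of zero.

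**Step 1: overlap of duration and calendar time.** Within a participant, calendar time = entry date + duration, so the correlation is exactly 1. Across participants, staggered entry loosens it:
- Var(duration) = (1 + 9 + 36)/3 − (10/3)² = 15.33 − 11.11 = 4.22
- Var(entry) = 6²/12 = 3
- r = √(4.22/7.22) = 0.76

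The two are strongly but not completely confounded.

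**Step 2: bias when calendar time is omitted.** Let usability improve by g SD per calendar month. The expected score is a + β·duration + g·(entry + duration). With complete visits, entry has the same distribution at every visit, so the fitted slope on duration is β + g. The false month 1 to 6 change is 5g:

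| g (SD per month, assumed) | False change, month 1 to 6 |
|---|---|
| 0 | 0 |
| 0.05 | 0.25 SD |
| 0.1 | 0.5 SD |

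For scale, the 95% half-width of a paired change is 1.96·√(2(1 − ρ)/32), where ρ is the between-visit correlation. It is 0.49 SD at ρ = 0, 0.35 at ρ = 0.5 and 0.22 at ρ = 0.8.

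**Step 3: discrete releases.** A random-intercept model was simulated (2,000 runs per scenario) with releases at calendar month 6; at 3, 6 and 9; or at 2, 4, 6, 8 and 10. A gain of 0.2 points per release is assumed for columns 3 and 4.

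| Releases | Within-person correlation, duration with release | False month 1 to 6 change | Declared significant | SE ratio once release is added |
|---|---|---|---|---|
| 1 | 0.80 | 0.17 | 21% | 1.6 |
| 3 | 0.95 | 0.34 | 60% | 2.5 |
| 5 | 0.98 | 0.50 | 92% | 2.7 |

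With no gain per release, about 5% of runs are significant. With gains of 0.1 to 0.3 the false change runs from 0.08 to 0.26 (one release), 0.17 to 0.51 (three) and 0.25 to 0.76 (five). Adding release number returns the estimate to between −0.01 and +0.01 in every scenario.

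**Step 4: price of adjustment.** Under the simulated SDs the unadjusted SE of the month 1 to 6 change is 5 × 0.6/√(32 × 3 × 4.22) = 0.149, a half-width of 0.29. Multiplying by the SE ratios gives about 0.5, 0.7 and 0.8 for one, three and five releases.

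Adjusting for linear calendar time instead, the variance ratio is 1 + 4.22·(σb²/σe² + 1/3), where σb² and σe² are the between-person and residual variances. The SE ratio is then 1.55 at within-person correlation 0, 2.1 at 0.3, 2.6 at 0.5 and 3.1 at 0.64. The 1.55 is therefore a floor that applies only if repeated visits were independent.

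**Step 5: a form of adjustment to avoid.** Assessment date = enrolment date + visit month. Entering both dates as linear terms beside visit is exactly collinear.

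**The case against.** The strongest reply has four parts.

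- **Deployment is inferred.** The text says when data are obtained, not when changes go live. If every change came after the last visit there would be no confounding. This stands, and the point is conditional on it. The iterative wording, the Study Monitoring heading and the inclusion of the questionnaire schedule make in-study deployment the natural reading.
- **No time-trend hypothesis is declared.** The outcome is usability and acceptability, duration is listed as a covariate, and no reason is given for the 1, 3 and 6 month visits. A reader might infer that the study sets out to show that acceptability lasts, or that a positive slope would be reported as habituation; the article says neither. What remains is that the planned model estimates a duration effect, and pooled scores also mix versions.
- **This is a condensed article.** Full model terms and a version log may sit in documents not shown. That is fair, so the point rests on what the article does state: a plan to change the system in order to improve usability, beside a named covariate list that does not reflect it.
- **Iterative development is legitimate in a 32-person feasibility study.** This stands too. The interviews and recorded monitoring contacts also give direct evidence on why views change. It is a reason not to demand a frozen platform, but not a reason to leave the version unrecorded.

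**Conclusion.** The point holds conditionally. If changes reach enrolled participants, the plan as written lets any release gain load on the duration effect. The mechanism follows from the article's own design plus assumed staggered entry. The size does not: 0 to 0.5 SD from month 1 to 6 rests on an assumed gain of 0 to 0.1 SD per month, and the simulated figures rest on assumed SDs, gains and release counts.

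Two stronger readings are not supported. A reader might conclude that the study cannot say which system its scores describe. But assessments fall at scheduled visits, so scores could be matched to a release history if one is kept, and staggered entry makes release and duration partly separable. A reader might also conclude that the seizure models are compromised. Wearable and phone-sensor data are collected continuously, so a questionnaire-schedule change would touch only the active features, and nothing in the article allows that effect to be sized.

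**What to change.** 1. Record the app and platform version and the questionnaire schedule in use at each PSSUQ and TAM-FF assessment.
2. Report scores by release.
3. Add release as a time-varying term beside visit in a sensitivity analysis. Do not enter linear enrolment date and linear assessment date together with visit.
4. Present the time trend as descriptive unless it survives this adjustment.

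Alternatively, if changes are to be deployed only after follow-up, say so in Study Monitoring; that one sentence removes the problem.

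The cost is a version log and one extra analysis. The adjusted estimate will be imprecise at n = 32, because of the SE increases shown in the working. Fewer releases would separate the effects better, but bundling or freezing them is optional, since it trades against the iterative development the study declares.

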### Study Withdrawal

There may be several reasons for withdrawal from the study. Participants were free to withdraw from the study at any point without providing reasons. The research team may withdraw the participant in the event of intercurrent illness, adverse events, protocol violations, and administrative or other reasons. In the case of participant self-withdrawal, all attempts will be made to have a face-to-face appointment with the participant to establish the cause of withdrawal and to collect qualitative data regarding the experience of participation. All data, including those from study withdrawals (unless participants request for deletion of their data), will be included in the final analysis.

### Data Handling and Confidentiality

All digital and nondigital information related to study participants will be nonidentifiable, in accordance with the General Data Protection Regulation. Each participant will be assigned a sequential identification number, used to collect, store, and report participant information. Data acquired from the wearable devices and from the apps will be encrypted, anonymized, and uploaded automatically via Wi-Fi to secure servers and infrastructures (RADAR platform) managed by the research team.

### Statistical Analysis Plan

Descriptive statistics for demographics, attrition rate, and number of participants using remote assessment measurements will be estimated. The primary outcome measurement (PSSUQ and TAM-FF) will be analyzed using a mixed-effect model for repeated measures based on observed case data. The model will include the duration in the study and contextual variables (CSRI, LTE-Q, etc) as covariates. Using classification approaches, we will investigate whether any demographics and/or other numerical information might serve as a predictor for subjects dropout. Using mixed-effect models with participants as a random factor, we will estimate whether there is a univariate relationship between the amount of RMT usable data during the weeks before the outcome assessment and obtained scale measurements (PSSUQ and TAM-FF). Acoustic features such as pitch, jitter, shimmer, formants, and intensity of the voice will be extracted from the speech task and will be analyzed.

To assess seizure detection performance of a multiparametric wearable system, we will relate seizures detected by the wearable system to the information from the seizure diary, kept by each participant. We will estimate the sensitivity of seizure detection by the wearable system (ie, whether all seizures reported in the diary were detected by wearable system) and false alarm rate (ie, number of seizures detected by the wearable system but not reported in the diary per unit of time, eg, day).

We will develop an analysis strategy for managing multi-sensor data. To this end, we will investigate what type of features derived from the pRMT and aRMT correlate with seizure occurrence and frequency per unit of time (eg, day and week). Seizure occurrence and frequency will be derived from the multiparametric wearable system and from seizure diaries and analyzed separately. Data obtained from wearable biosensors will be used to derive information about participants’ activity during the day and information about sleep and mood. Aggregated features obtained from biosensors, smartphones, and cognitive tests and from ESM and their changes from baseline or previous time points (delta features) will be used for statistical analysis. First, we will use a univariate approach, where the number of seizures per unit of time will be modeled with each variable or feature as a fixed effect and participant as a random effect. Demographics and other baseline characteristics will be added to the model when necessary. Correction for multiple comparisons will be taken into account. Second, using aggregated data obtained through some time duration to predict the number of seizures per the same time duration, we will construct predictive models. Under the assumption that data are missing at random, multiple imputation will be applied for covariates, where missingness is not drastically high. Multivariate prediction models will be constructed, and variable selection, based on, for example, least absolute shrinkage and selection operator L1-regularization for linear models, or different feature selection algorithms will be applied. Model performance will be characterized through cross-validation, putting stress on the sensitivity and specificity of the predictive model.

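### The PSSUQ and TAM-FF analysis has no score from people who leave before week 4 and takes later leavers' missing scores as missing at random, which favours the technology if leaving reflects low acceptability

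*Protocol article*

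**What the plan says.** - **Primary outcome (Study Outcomes).** "The primary outcome of interest was participants’ acceptability and usability of the RADAR technology, including the wearable, the apps, and the assessment scheme". It has three instruments: PSSUQ, TAM-FF and "ad hoc created qualitative interviews undertaken at 1, 3, and 6 months postenrollment".
- **Timing (Table 1).** PSSUQ and TAM-FF are ticked at weeks 4, 12 and 24. There is no baseline score and no withdrawal column.
- **Model (Statistical Analysis Plan).** The two questionnaires "will be analyzed using a mixed-effect model for repeated measures based on observed case data". On covariates: "The model will include the duration in the study and contextual variables (CSRI, LTE-Q, etc) as covariates". By Table 1, CSRI and LTE-Q are also taken only at weeks 4, 12 and 24.
- **Leavers (Study Outcomes, Study Withdrawal).** "Participants who dropped out before the study endpoint will be contacted to complete an interview". For people who withdraw themselves, a meeting is sought "to establish the cause of withdrawal and to collect qualitative data regarding the experience of participation". Neither section mentions PSSUQ or TAM-FF. Study Withdrawal adds: "All data, including those from study withdrawals (unless participants request for deletion of their data), will be included in the final analysis".
- **Missing data (Statistical Analysis Plan).** Attrition will be described and predictors of dropout explored, but neither is linked to the questionnaire estimate. Missing at random is named only with multiple imputation of covariates in the seizure prediction models.

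**The concern.** A likelihood-based repeated-measures model on observed cases is valid when missingness depends only on what has been observed. That condition is doubtful here, because the outcome is acceptability and stopping can be an expression of low acceptability. The article itself makes a link of this kind: its Discussion says that false alarms can harm acceptance and long-term use.

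Two groups are affected. People who leave before week 4 have no score, so the model cannot draw on them at all. People who leave after week 4 or week 12 keep their earlier scores, but the model predicts their later course from participants with similar earlier scores who stayed. If a drop in opinion is what made them leave, that prediction is too kind.

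At stake are the level of the questionnaire means and, to a smaller degree, their change over time. Any error favours the technology under study.

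**Working it through.** **Inputs from the document.** 32 participants ("32 individuals with a diagnosis of epilepsy will be asked to download several RMT apps"); ratings at weeks 4, 12 and 24; observed-case mixed model. The article gives no SD, dropout rate or derivation of the sample size, so there is no stated figure to reproduce. Every dropout and score input below is an assumption.

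**Step 1: people never rated.** Let d be the share who leave before week 4 and Δ how much worse, in SD, they would have scored.

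Bias of the observed mean = d × Δ in favour of the technology; its standard error ≈ 1/√(32(1 − d)) SD.

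| d | people of 32 | Δ = 0.5 | Δ = 1.0 | Δ = 1.5 | SE |
|---|---|---|---|---|---|
| 10% | 3.2 | 0.05 | 0.10 | 0.15 | 0.19 |
| 20% | 6.4 | 0.10 | 0.20 | 0.30 | 0.20 |
| 30% | 9.6 | 0.15 | 0.30 | 0.45 | 0.21 |
| 40% | 12.8 | 0.20 | 0.40 | 0.60 | 0.23 |

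This table covers only people with no rating at all. It must not be read with total dropout in place of d.

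**Step 2: dropout spread over the three visits.** A large-sample simulation fitted an unstructured normal likelihood to three visits, which is equivalent to the planned type of model without covariates. Assumptions: correlation 0.6 between visits, a true mean that is constant over time, and permanent dropout whose log-odds rise by 0, 1 or 2 per SD of worse current, unobserved score. With a slope of 0 the bias was zero at every visit and every dropout rate. With slopes of 1 and 2 (lower and upper end of each range), the bias in favour of the technology, in SD, was:

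| Total dropout | Never rated | Week 4 | Week 24 | Spurious change, week 4 to 24 |
|---|---|---|---|---|
| 10% | 3–4% | 0.03–0.06 | 0.04–0.08 | 0.01–0.02 |
| 20% | 8% | 0.07–0.12 | 0.09–0.16 | 0.02–0.04 |
| 30% | 12–13% | 0.11–0.18 | 0.14–0.23 | 0.03–0.05 |
| 40% | 17–19% | 0.14–0.25 | 0.20–0.32 | 0.06–0.07 |

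The last column is week 24 minus week 4, for example 0.16 − 0.12 = 0.04. Most of the bias is already in the level at week 4, where the never-rated are missing; the trend is affected less.

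**Step 3: effect of rating people at withdrawal.** Suppose 70% of leavers give a score at withdrawal, that it equals the score they would have given at the first missed visit, and that it is entered there. Week-24 bias then falls to 0.02–0.05 SD at 20% dropout (from 0.09–0.16) and to 0.05–0.09 SD at 40% (from 0.20–0.32).

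**The case against.** The strongest reply is that leavers are not ignored. Interviews are one of the three instruments of the primary outcome, dropouts are to be interviewed, and Qualitative Data Analysis describes a thematic analysis of the interviews. Attrition is reported and predictors of dropout are sought. All of this stands. A reader might infer that leavers are left out of the primary answer; the document does not support that. What remains is that thematic findings cannot correct a questionnaire mean or its time course.

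Other stronger readings also fail:

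- **That the result describes only those who stayed.** That would be a completers analysis. This model keeps the scores that later leavers gave and is unbiased if dropout depends only on those scores.
- **That the observed-case model contradicts the promise to use withdrawals' data.** That promise concerns data that were collected, and the model uses them.
- **That the bias is 0.20 SD or more at 20% dropout.** With leavers 1 SD worse, this needs 20% of the cohort to leave before the first rating, despite a 60-minute training session and a call at week 2. With dropout spread over the visits, the figures in step 2 apply.
- **That every withdrawal is a rejection of the technology.** Study Withdrawal also lists intercurrent illness, adverse events, protocol violations and administrative reasons. Counting use as zero after every withdrawal would misclassify these, and usage data may not exist for all, since participants can have their data deleted.

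The article is also a condensed account. A questionnaire at withdrawal or a sensitivity analysis may be in the full protocol or analysis plan, so the absence of a sensitivity analysis here is not an error. Finally, the study has no stated acceptability threshold or comparison group, so the bias cannot overturn a stated decision rule.

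**Conclusion.** The point holds for the questionnaire part of the primary outcome. As described, PSSUQ and TAM-FF have no score from people who leave before week 4, later missing scores are taken as missing at random, and views after leaving enter only through interviews. If leaving depends on low acceptability beyond what earlier scores show, the means and, less strongly, the trend are biased in favour of the technology.

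Under the assumptions in step 2, the week-24 bias is about 0.09 to 0.16 SD at 20% total dropout and 0.20 to 0.32 SD at 40%. A simple mean of those observed has a standard error of roughly 0.20 to 0.23 SD at these rates, so the bias lies below sampling error at 20% dropout and can exceed it at 40%. It is zero if dropout is unrelated to the score. The direction is secure when dropout depends on the unobserved score; the size rests on an assumed dropout rate, correlation and strength of dependence. This is a cheap improvement to make, not a flaw that invalidates the primary outcome.

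**What to change.** 1. Give PSSUQ and TAM-FF at the withdrawal contact already planned in Study Outcomes and Study Withdrawal, by telephone or web if a face-to-face meeting is not possible. Enter the ratings in the model at the time of withdrawal, and state beforehand how that time maps to the visit schedule.
2. Because CSRI and LTE-Q are model covariates scheduled only at weeks 4, 12 and 24, collect them at the same contact or state how they will be handled. Otherwise a withdrawal rating may lack the covariates it needs to enter the model.
3. Report attrition, with reasons, beside the questionnaire scores at each visit.
4. Add a sensitivity analysis that shifts unobserved ratings in the unfavourable direction, for example by 0.5, 1.0 and 1.5 SD, for withdrawals related to the technology. The recorded cause of withdrawal identifies these. If the full analysis plan already contains such an analysis, no change is needed.

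The cost is slightly more participant burden at a contact that takes place anyway, one extra table, and possibly a less favourable acceptability result. Ratings not taken at withdrawal are hard to recover later, so this should be settled before data collection ends.
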